**SPONSOR**

Western Sydney University through NICM Health Research Institute

[name]

[name]

This is an investigator initiated study led by [name] who is a WSU employee. [name] and the rest of the team have taken on responsibilities of sponsor and investigator roles. [name] retains full control over study design, data collection, study management, analysis and interpretation of the data, writing of the report, and submitting the report for publication.

**SOURCES OF FUNDING**

NHMRC CRE in PCOS Project Grant 2017 (Competitive grant)

Partnership grant – Neural Ear Stimulation International (NESI) and NICM HRI (Non competitive grant – consultancy)

Chief Investigators of the CRE in PCOS are included as investigators in this study (CIs [name] and [name]). This was a criteria for grant eligibility. However, the CRE in PCOS in itself will not have any role in study design, data collection, study management, analysis and interpretation of the data, writing of the report, or submitting the report for publication apart from the involvement of the two CIs.

NESI provides advice on the use of the Neurova device, including suggested frequency of treatment, and acupuncture points to be used, but does not otherwise play any role in study design, data collection, study management, analysis and interpretation of the data, writing of the report, or submitting the report for publication

**TRIAL REGISTRATION**

Australian New Zealand Clinical Trial Registry, ACTRN12618000975291 08/06/2018

**DECLARATION OF INTERESTS**

CE declares that she is a practising acupuncturist. As a medical research institute, NICM Health Research Institute receives research grants and donations from foundations, universities, government agencies, and industry. Sponsors and donors provide untied and tied funding for work to advance the vision and mission of the Institute.

**Summary**

*Professional Summary*

This feasibility study on acupuncture for weight loss in Polycystic Ovary Syndrome (PCOS) is a collaboration between the National Institute of Complementary Medicine/Western Sydney University, the PCOS Centre for Research Excellence, Jean Hailes for Women’s Health, GetHealthyNSW and IVF-Australia and aims to assess feasibility and acquire data to inform a fully-powered trial for submission to nationally competitive funding agencies. This study is also a partnership with Neural Ear Stimulation International (NESI Corp).

*Lay Summary*

Polycystic Ovary Syndrome (PCOS) is a common women’s health hormonal problem that can result in irregular periods, infertility, weight gain, acne and excess body hair, and anxiety and depressive symptoms. Weight loss can improve these symptoms, however many women find this difficult to achieve. Acupuncture is a Chinese medical treatment that involves insertion of very fine metal needles into specific areas of the body, and has been shown to help obese and overweight adults lose weight, however few studies have been conducted in women with PCOS. A variant of acupuncture, called auricular electro-acupuncture (electrical stimulation to points on the ear) may have beneficial effects on "fight or flight" syndrome which is associated with PCOS. This study aims to collect preliminary information on whether it is possible and acceptable to perform clinical research on acupuncture and/or auricular electro-acupuncture for weight loss in PCOS women. We are partnering with IVF-Australia, a leading fertility organisation in Australia, to recruit women for this study. We aim to analyse 30 women in this clinical trial. Women will be randomly allocated to receive one of three types of treatments: acupuncture as well as a telephone-based lifestyle coaching; AEA and telephone-based lifestyle coaching; or telephone-based lifestyle coaching alone. We will measure women’s weight before and after treatment and investigate the possible ways that acupuncture and AEA may benefit weight in PCOS, including measuring heart rate variability and insulin levels. The findings from this study will help us design a larger trial that will provide more definitive answers as to whether acupuncture or AEA is an effective treatment for weight loss. If acupuncture helps women with PCOS lose weight, this means that these women will have improved chances of having a baby, more regular periods, and a lower risk of developing diabetes and heart disease in the future.

**Study Synopsis**

| **Title:** | **Acupuncture or auricular electro-acupuncture as adjuncts to lifestyle interventions for weight management in PCOS: a randomised controlled feasibility study** |
| --- | --- |
| **Sponsor:** | **NHMRC CRE in PCOS (Project Grant)** |
| **Protocol Number:** | **V12** |
| Development Phase: | Phase II |
| Indication: |  |
| **Objectives of the Study:**  Primary Objective: | Determine feasibility and acceptability of study procedures |
| Secondary Objective(s): | Determine an effect size for acupuncture and lifestyle vs AEA and lifesyle vs lifestyle alone and examine for a trend between groups for change in body weight, BMI, Heart Rate Variability and insulin sensitivity |
| **Study Drugs/Therapeutic Intervention:** | Acupuncture and telephone-based lifestyle intervention compared to AEA and telephone-based lifestyle intervention compared to telephone-based lifestyle intervention alone |
| **Study Design**: | Randomised controlled feasibility study |
| **Study Endpoints** (primary and secondary) | Primary: Recruitment, retention, adherence, acceptability , credibility and safety over the recruitment and intervention periods.  Secondary: Difference between groups for anthropometric measures, blood pressure, health-related quality of life, menstrual cycles, psychological measures, self-efficacy and locus of control, heart rate variability, insulin, glucose, Sex Hormone Binding Globulin, total and free testosterone and free androgen index |
| **Sample size** (by treatment group):  Sample Size Determination: (If applicable) | We aim to analyse 30 women (10 in each group) at the end of treatment |
| **Total Number of Study Centres** | 1 |
| **Study Duration:** | 12 weeks |
| **Inclusion Criteria:** | - women aged 18-45 years - physician diagnosis of PCOS according to the 2003 Rotterdam Criteria in previous 5 years[14]; - BMI≥25 kg/m^2^; no other endocrine disorders; - not pregnant/no pregnancies in preceding 6 weeks and more than 6 weeks postpartum; - not on the following medications in the 3 months preceding enrolment: metformin or other medications affecting insulin and glucose metabolism, hormonal treatments for PCOS/ART including gonadotrophins and the Oral Contraceptive Pill, pharmaceutical or complementary therapies for weight loss |
| **Exclusion Criteria:** | - Planning to conceive within the next 3 months - Needle acupuncture in the previous 3 weeks - Unable to provide informed consent. - BMI >40 - anticoagulant use - pacemaker use - immunocompromise - valvular heart disease - Currently breastfeeding or have ceased breastfeeding within the past 6 weeks ( a waiting period may apply) |
| **Dosage Regimen/Duration of Treatment:** | 12 treatments of acupuncture over 12 weeks, twice a week for 4 weeks then fortnightly after |
| Investigational Product/Therapy 1: | Acupuncture and telephone-based lifestyle interventions |
| Investigational Product/Therapy 2: | Auricular Electro-acupuncture (AEA) stimulation and telephone-based lifestyle interventions |
| Control Group: | Telephone-based health coaching |
| **Study Procedures:** | The majority of outcomes will be completed at the pre and post intervention visit. Participants will wear an accelerometer at -1 and 11 weeks for 5-7 days and will complete a menstrual calendar. |
| **Statistical Analyses:** (Brief Description) | Descriptive statistics for primary endpoint. |

# Introduction

## Background

This feasibility study on acupuncture for weight loss in Polycystic Ovary Syndrome (PCOS) is a collaboration between NICM/Western Sydney University, the PCOS Centre for Research Excellence, Jean Hailes for Women’s Health, GetHealthyNSW and IVF-Australia and aims to assess feasibility and acquire data to inform a fully-powered trial for submission to nationally competitive funding agencies. A Partnership with NESI Corp is allowing for the addition of a third comparative arm, using auricular electro-acupuncture.

***Polycystic Ovary Syndrome and obesity/overweight:***

PCOS is a common women’s health condition with significant reproductive, metabolic and psychological manifestations such as infertility and Type 2 Diabetes (T2D)[1]. Women with PCOS are more likely to be obese/overweight than age-matched controls[2], and excess weight worsens the features of PCOS[3]. Weight loss is a key goal in PCOS, and lifestyle management (diet, exercise, and/or behavioural interventions) targeted at weight loss are first-line recommendations in overweight/obese women[3] as even modest weight loss improves reproductive and metabolic outomes. Current evidence-based guidelines on PCOS recommend that obese women embark on 3-6 months of lifestyle management for weight loss prior to considering Assisted Reproductive Technology (ART). However, adherence is generally low[3], and achieving adequate weight loss remains a significant challenge [2].

**The potential role of acupuncture**

In non-PCOS populations, acupuncture is more efficacious than sham for weight loss, with mean differences in body weight and Body Mass Index(BMI) of 1.58kg[4] to 4.4kg[5], and 0.6 kg/m^2^[4]to 2.79 kg/m^2^[6] respectively (3.5-5% decrease from baseline)[4-7]. These effects are mediated through alterations in obesity-related peptides, appetite regulation, insulin levels, free fatty acids and inflammatory markers[8] and are sustained after end-of-treatment[5]. RCTs conducted in China indicate that acupuncture + metformin is superior to metformin alone in women with PCOS for reducing BMI[9]. The overall effect size is unclear, although one study reported a mean difference of 0.97kg/m^2^ (95% CI 1.51, 0.43) for acupuncture + metformin compared to metformin alone[10].

**Could acupuncture be an effective adjunctive weight loss treatment via modulation of sympathetic tone?**

Although the exact etiology of PCOS is unknown, *insulin resistance* (IR) is a key factor and contributes to obesity [13]. *Increased sympathetic tone* is an associated factor of IR [14] and has been identified as a potential therapeutic target in PCOS[15]. In rats with steroid-induced PCOS, electro-acupuncture reduces ovarian sympathetic hyper-innervation, ameliorates IR, and improves oestrous cycling[16]. Electro-acupuncture reduced Muscle Sympathetic Nerve Activity in PCOS women in one trial[14]. Our qualitative work indicates high levels of acceptance of acupuncture as a possible adjunct to lifestyle interventions for weight loss, and subsequently we have secured external funding and Ethics approval for a feasibility study comparing acupuncture and lifestyle interventions (Phase 2b of our research program; see Figure 1; n=20)

**Auricular Electro Acupuncture stimulation: a novel approach to delivering protracted acupuncture?**

A variant of acupuncture is Auricular Electro-Acupuncture (AEA). Our partner has shown that AEA (delivered by the Neurova device) is effective for hot flushes from androgen-deprivation therapy, a condition underpinned by sympathetic hyperactivity[1]. This method involves insertion of indwelling needles into the concha of the ear and delivery of intermittent electrical impulses over 96 hours by a small battery-powered device that is worn just below the ear. This significantly increases the "dose" of acupuncture that can be delivered ("protracted acupuncture").

Evidence suggests that AEA stimulates the auricular branch of the vagus nerve, *increases parasympathetic tone*[18], suppresses the appetite[17] and produces *sympathetic deactivation* [19]. Through this reasoning we expect to improve autonomic function that contributes to improved IR and resultant weight loss.

**Heart Rate Variability: a surrogate marker of autonomic tone**

Sympathetic tone can be measured directly using microneurography; however, this procedure limited by its invasive nature. Heart rate variability (HRV) provides non-invasive measures of both parasympathetic (high frequency/HF component) and sympathetic tone (low frequency/LF component) [16, 18]. Several sham-controlled RCTs on acupuncture for a variety of clinical conditions suggest that it is more efficacious than sham in reducing sympathetic tone as measured by HRV[18-20]. To date, the effect of acupuncture on HRV in women with PCOS has not been evaluated, although electro-acupuncture improved HRV and restored oestrous cycling compared to sham handling in a recent rat study[21].

Our partner's previous research showed that AEA resulted in improvement in HRV LF/HF ratios over the course of the protocol intervention, implying improved sympathovagal balance[1], however this was measured using ambulatory HRV monitoring, which has not been validated against the gold-standard of electrocardiogram (ECG) recordings.

## Rationale for Study

Acupuncture may represent a low-risk[11] non-pharmacological adjunct to lifestyle interventions, but to date no sham-controlled trials have been conducted on acupuncture for weight loss in PCOS. Many randomised controlled trials (RCTs) fail due to inability to recruit to target[12]. To this end, the UK Medical Research Council recommends assessment of feasibility prior to full evaluation of complex interventions[13]. This can ensure that money spent on expensive trials is not wasted due to recruitment and retention failures.

PCOS is the leading cause of anovulatory infertility, and obesity increases the prevalence of infertility and pregnancy complications, as well as metabolic complications such as T2D and cardiovascular disease. Management of these complications is estimated at $800 million annually in Australia[1].

# Study Objectives

## Objectives

### Primary Objective

(1) Assess recruitment, retention and adherence rates and acceptability of trial procedures

### Secondary Objectives

2) Determine an effect size for acupuncture and lifestyle vs lifestyle alone and examine for a trend between groups for change in body weight and BMI.

3) Explore the impact of body electro-acupuncture and auricular electro-acupuncture on sympathetic tone and insulin resistance

## Endpoints

### Primary Endpoint

Recruitment, retention and adherence rates; credibility; acceptability; and safety over the recruitment and intervention periods.

### Secondary Endpoints

Difference between groups for anthropometric measures, health-related quality of life, menstrual cycles, psychological measures, self-efficacy and locus of control; measures of insulin resistance; and heart rate variability; free and total testosterone and free androgen index.

# Study Design

This is a prospective open-label parallel randomised controlled feasibility study taking place over a 12 week intervention period.

# Study Population

## Number of Participants

We aim to analyse 30 participants by the end of treatment. Allowing for a 25% dropout rate which has been reported in similar studies, we will randomise 39 women (13 to real acupuncture, 13 to AEA and 13 to lifestyle alone).

### Inclusion Criteria

- women aged 18-45years;
- physician diagnosis of PCOS according to the 2003 Rotterdam Criteria in previous 5 years [14];
- BMI≥25 kg/^2^; no other endocrine disorders;
- not pregnant/no pregnancies in preceding 6 weeks and more than 6 weeks postpartum;
- not on the following medications in the 3 months preceding enrolment: metformin or other medications affecting insulin and glucose metabolism, hormonal treatments for PCOS/ART including gonadotrophins and the Oral Contraceptive Pill, pharmaceutical or complementary (nutritional/herbal) treatments for weight loss

### Exclusion Criteria

- Planning to conceive within the next 3 months
- Needle acupuncture in the previous 3 weeks
- Unable to provide informed consent.
- BMI >40
- anticoagulant use
- pacemaker use
- immunocompromise
- valvular heart disease
- Currently breastfeeding, or breastfeeding within the last 6 weeks

# Participant Selection And Enrolment

## Identifying Participants

### Recruitment sources

Women living in Sydney will be recruited via

- IVF-Australia fertility clinics and specialty PCOS clinics (brochures and fliers displayed at clinics, and recruitment by clinicians who wish to be involved);
- PCOS Association of Australia,
- Jean Hailes for Women’s Health and other women’s health or health or community online sources
- Fliers at strategic places in the community such as fitness centres
- social media
- Gethealthy NSW
- Study webpage hosted on the National Institute of Complementary Medicine’s website with a description of the trial, the Participant Information and Consent Form, Ethics approval details, contact details for the Research assistant and for [name], and a link to an online survey where participants can self-screen for eligibility
- Western Sydney University staff and student portals

### Procedure for identifying participants

A proxy website will be created with a memorable URL that will redirect potential subjects to the official study webpage. A Facebook page will be created that will post study updates and contain a link to the study webpage.

Women will be either be invited to the study by a clinician working at IVF-Australia clinics, or self-refer after viewing details on brochures and fliers displayed in clinics, and online advertisements via Jean Hailes, PCOS Association, social media and other online sources such as university newsletters. Women can complete an online survey to self-screen, or be screened over the telephone by the research assistant.

Clinicians who agree to be involved in recruitment at IVF-A will be provided with brief information about the study and a brochure inviting the patient to take part. Clinicians will identify potentially eligible women either at the time of consultation, or through an audit of clinic patients. Patients identified by audit will be mailed a letter from the clinician with brief details about the study, and a brochure and the Participant Information and Consent Form, and will be encouraged to call, email or self-screen using the online survey to check eligibility.

GetHealthyNSW telephone operators will be provided brief details about the study, eligibility criteria, and will invite potentially eligible callers to the study by providing them with brief information and obtaining consent for the research assistant to contact the participant by phone or email. They will also be provided with the online survey link in order to self-screen if they wish.

Brochures and fliers will also be displayed at Western Sydney University campus sites, GP clinics and other community sites such as fitness centres and community health centres.

Withdrawal criteria: Women can withdraw at any time and their data will be removed from the study upon their request.

## Consenting Participants

At the time of confirming eligibility, women are provided with Participant Information and Consent Form and are also provided with verbal information about the trial from either [name] or the Research Assistant. Participants are given sufficient time to read the PICF and ask questions. It is anticipated that in the most part participants will be provided the PICF by email or mail, and verbal information over the telephone. Following which an appointment is made for the baseline clinic visit OR the participant is given time to make a decision and the Research Assistant will contact her within a week to enquire of the decision. Once the participant decides to enrol in the trial, verbal consent is obtained in order to start collecting data for the run-in period which includes having a blood test for an OGTT, and wearing an accelerometer for 5-7 days prior to the baseline visit.

At the baseline/pre intervention clinic visit, participants are given another opportunity to ask questions prior to providing written consent to participate in the trial. At that point, the participant is enrolled into the trial and is assigned a study ID number and is randomised.

Written consent will be obtained either by the Research Assistant or [name]. If [name] is not able to be present at the time of written consent, she will telephone the participant beforehand to answer any questions that pertain to acupuncture treatment and risks.

## Screening for Eligibility

Participants have to meet the eligibility criteria described in 4.1.1 and 4.1.2. This is performed using the Screening Survey which can be administered over the telephone by the Research Assistant, or self-reported using a paper or electronic survey. Potential subjects may self-screen using the online survey. If they are eligible, they are asked to provide contact details (name, and two telephone numbers, and an email address). The research assistant will then contact the participant initially by email (providing the participant with details of the next steps, the PICF, and contact details). The research assistant will also call the participant to arrange a baseline/pre intervention clinic visit.

Enrolment into the trial requires diagnosis of PCOS by a physician in the previous five years. Women are asked to confirm if they have been diagnosed by a physician in the last five years (GP, Endocrinologist, Gynaecologist) and if they meet the Rotterdam criteria. [name] will make contact with all potentially eligible participants following completion of the screening survey, and confirm the diagnosis, which may involve viewing de-identified ultrasound or pathology reports. Women will be asked to de-identify their own reports by removing all identifiers on their report such as name, date of birth, and address using a marker pen. They will then fax or email the de-identified reports to [name] university email address or office fax. Alternatively, they can request for pathology providers or radiology providers to securely transmit reports to [name] private GP clinic. This process mimics usual clinical practice and is convenient and secure.

It is unlikely that women will need to provide previous reports as the majority of them are anticipated to be diagnosed according to clinical criteria (menstrual irregularity, signs of hyperandrogenism such as hirsutism or male pattern balding). If women do not have reports within the last five years and do not have current signs or symptoms of PCOS, they will be asked to see their GP to have the diagnosis confirmed by pathology/ultrasonography, or refuted. This is relevant as some women may no longer have PCOS (for example, if they lose weight) and therefore will not require treatment.

The diagnosis is made or confirmed by [name] if women are currently still having symptoms and signs of PCOS (i.e. oligomenorrhoea and/or clinical hyperandrogenism), and were symptomatic at the time of having abnormal pathology and radiology reports (if relevant).

The medical records that women may need to obtain for [name] perusal include:

- testosterone, free testosterone, Sex hormone binding globulin, free androgen index levels
- pelvic ultrasound reports
- Thyroid function tests

Rotterdam Criteria:

Two out of three of:

a. Menstrual cycles greater than 35 days apart OR shorter than 21 days apart^1^

b. Clinical (hirsutism, male pattern balding) or biochemical hyperandrogenism^2^ (testosterone and/or free androgen index)

c. Polycystic ovaries on ultrasonography when >18yo^3^ ( ten or more small antral follicles in both ovaries)

^1^Thyroid disorders should be excluded

^2^ If androgen levels are markedly elevated (testosterone levels >20% over upper limit) or there was rapid or sudden onset of hyperandrogenism, congenital adrenal hyperplasia or rarer causes of hyperandrogenism should be excluded by performing a serum 17-hydroxyprogesterone level in the follicular phase and also by endocrinology review

^3^If ultrasonography was conducted when the woman was an adolescent, results are to be interpreted with caution. Vaginal ultrasounds are desirable, but abdominal US can be considered for use in diagnosis.

If participants are screened by the research assistant, this is done over the telephone and if eligible the participant is invited to attend for a baseline clinic visit.

Participants are also required to have an Oral Glucose Tolerance Test (OGTT )done as part of the outcomes of the study. The baseline OGTT will be done prior to enrolling the participant, as diagnosis with Type 2 diabetes or impaired glucose tolerance (both of which can be diagnosed from the OGTT) is an exclusion criterion. [name] will contact the participant to inform them of their results and eligibility to join the trial. If the participant is diagnosed with diabetes or impaired glucose tolerance, they are referred to their GP for further management, and are not eligible to enrol for the trial.

All women will be offered the opportunity to have their diagnosis of PCOS re-confirmed through blood tests done at baseline. This is *only* offered to women who have had an initial diagnosis of PCOS made by a doctor at any stage. Women are offered the opportunity to have the following blood tests to confirm the diagnosis: TSH and/or Prolactin, Free Androgen Index, Free and Total Testosterone. The latter two tests are already performed at baseline, but they can be used as a screening test if required.

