The auricular ear-acupuncture stimulation device has not been trialled in pregnancy. Due to this lack of safety data, any woman intending on falling pregnant during the intervention period is to be excluded. Women are asked to avoid falling pregnant, and cease using the ear acupuncture device should they become pregnant.

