# Appendix 1 - Schedule of Observations and Procedures

| **Visit/Timepoint** | **Screening (self screening or telephone)** | **Week -1**  **(Run-in)** | **Visit 1**  **Baseline (Allocation)** | **1^st^ acupuncture treatment** | **Visit 2**  **Post intervention** |
| --- | --- | --- | --- | --- | --- |
| Week(s): | **-4 to -2** | **-1** | **0** | **1** | **12** |
| **ENROLMENT** |  |  |  |  |  |
| Eligibility screen | **X** |  |  |  |  |
| Informed Consent |  |  | **X** |  |  |
| 2hr OGTT and Insulin, free and total testosterone, SHBG, Free androgen index |  | **x** |  |  | **x** |
| Physical activity levels |  | **x** |  |  | **X (Week 11)** |
| Allocation |  |  | **X** |  |  |
| **INTERVENTIONS** |  |  |  |  |  |
| Body acupuncture + lifestyle |  |  |  |  |  |
| Auricular electro acupuncture + lifestyle |  |  |  |  |  |
| Lifestyle alone |  |  |  |  |  |
| **ASSESSMENTS** |  |  |  |  |  |
| Credibility and Expectancy Questionnaire |  |  |  | **X** |  |
| Demographic and medical questionnaire |  |  | **X** |  |  |
| Anthropometric measures and blood pressure |  |  | **X** |  | **X** |
| Concomitant Medications |  |  | **X** |  | **X** |
| Surveys – QoL, psychological, weight self efficacy, locus of control |  |  | **X** |  | **X** |
| Heart rate variability by ECG monitor |  |  | **x** |  | **x** |
| Ferriman-Gallwey score |  |  | **X** |  | **X** |
| Exit survey on acceptability of the intervention |  |  |  |  | **X** |
| Adverse Events |  |  | **X** | **X** | **X** |

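### The protocol specifies no objective or repeated check of current pregnancy before allocation, although non-pregnancy is an entry criterion and the ear device is untested in pregnancy

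*Protocol*

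**What the plan says.** **Criterion.** Protocol section 4.1.1 lists "not pregnant/no pregnancies in preceding 6 weeks and more than 6 weeks postpartum" among the inclusion criteria. Section 4.1.2 adds an exclusion based on intention: "Planning to conceive within the next 3 months".

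**How and when it is applied.** Section 5.3 says of the eligibility criteria: "This is performed using the Screening Survey which can be administered over the telephone by the Research Assistant, or self-reported". Appendix 1 marks the eligibility screen in one column only, weeks -4 to -2. Allocation is in the week 0 column.

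**Blood tests before allocation.** The Week -1 tests in Appendix 1 are "2hr OGTT and Insulin, free and total testosterone, SHBG, Free androgen index". The optional tests offered in section 5.3 to re-confirm the diagnosis are "TSH and/or Prolactin, Free Androgen Index, Free and Total Testosterone". Neither list contains a pregnancy test.

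**Safety statement.** Section 10.3 says: "The auricular ear-acupuncture stimulation device has not been trialled in pregnancy". It gives this as the reason for excluding women who intend pregnancy. It also asks participants to avoid pregnancy and to stop using the device if they become pregnant.

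**Allocation.** Section 4.1 randomises 13 women to each of three arms, so 13 of 39 receive the ear device.

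**The concern.** The protocol gives a reason to keep pregnant women off the device, yet it checks current pregnancy only through a survey that the woman may complete herself. Up to four weeks can then pass before the envelope is opened. The survey cannot detect a pregnancy that she has not recognised, or one that begins after she completes it.

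Self-report is also weaker than usual in this population. One of the three diagnostic features in section 5.3 is "Menstrual cycles greater than 35 days apart OR shorter than 21 days apart", and the same section expects most women to have been diagnosed on clinical criteria that include menstrual irregularity. For many of them a late period may give little warning. Section 4.1.1 bars the oral contraceptive pill for the preceding three months, and the protocol requires no other method in its place.

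The main stake is safety: a woman with an unrecognised pregnancy could be randomised to a device for which the protocol says it has no pregnancy data. A lesser stake is interpretation. Pregnancy could disturb secondary outcomes such as weight and menstrual cycles, and with 10 women analysed per arm, one woman is 1/10 = 10% of an arm.

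**Working it through.** **Step 1: does any later step before allocation check pregnancy?** The protocol states no figure on this point, so the check begins with the text.

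| Step | Stated purpose | Pregnancy check stated? |
|---|---|---|
| Screening Survey, weeks -4 to -2 (5.3, Appendix 1) | Apply the eligibility criteria | By self-report only |
| Investigator contact after the survey (5.3) | Confirm the PCOS diagnosis | No |
| Week -1 bloods (Appendix 1) | Glucose tolerance, insulin, androgens, SHBG | No |
| Contact with the glucose tolerance result (5.3) | Report the result and eligibility | No; concerns diabetes and impaired glucose tolerance |
| Optional diagnostic bloods (5.3) | Re-confirm PCOS | No |
| Visit 1 medical history (7.1.1) | Baseline description | No |
| Eligibility confirmed before the envelope is opened (5.5.1) | General condition for randomising | Not named |

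Diabetes and impaired glucose tolerance are excluded on a blood result obtained before enrolment, and the PCOS diagnosis is confirmed by an investigator. Pregnancy has neither kind of verification.

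**Step 2: the gap.** Weeks -4 to -2 against week 0 gives 2 to 4 weeks.

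**Step 3: illustrative size.** The documents give no conception rate. Assume a monthly probability p between 0.5% and 3%, and 4.345 weeks per month.

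- Per woman over w weeks: q = 1 - (1 - p)^(w/4.345)
- At least one among n women: P = 1 - (1 - q)^n

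| Gap | p | q | P, 13 device-arm women | P, all 39 women |
|---|---|---|---|---|
| 2 weeks | 0.5% | 0.0023 | 3% | 9% |
| 2 weeks | 3% | 0.0139 | 17% | 42% |
| 4 weeks | 0.5% | 0.0046 | 6% | 16% |
| 4 weeks | 3% | 0.0277 | 31% | 66% |

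The expected number of conceptions in the device arm over 4 weeks is 13 × 0.0046 = 0.06 to 13 × 0.0277 = 0.36. The table counts conceptions after the survey. It does not subtract those recognised before Visit 1, and it does not add pregnancies already present but unrecognised at the survey.

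**Step 4: a second route.** Assume instead that a proportion u of women have an unrecognised pregnancy at randomisation. Among 13 women, P = 1 - (1 - u)^13. For u = 0.25%, 0.5%, 1% and 2% this gives 3%, 6%, 12% and 23%.

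**Step 5: what a Week -1 assay cannot reach.** The last week before allocation is 1/4 of a 4-week gap and 1/2 of a 2-week gap. With w = 1 and n = 13, the chance of at least one conception in that week is 1.5% to 8.7% on the same assumptions. The true residual is larger, because an assay also misses a conception shortly before the sample. The 12-week intervention is three times as long as the 4-week gap, and a baseline assay does nothing about conceptions during it.

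**The case against.** The strongest reply is that the protocol recognises the risk and acts on it. Women planning to conceive are excluded in section 4.1.2, and section 10.3 adds the requests to avoid pregnancy and to stop the device. Eligibility is not closed at the survey either. An investigator contacts every potentially eligible woman, a second contact follows the glucose result, medical history is taken at Visit 1, and section 5.5.1 requires eligibility to be confirmed before the envelope is opened. The survey and the baseline questionnaire are not shown, so pregnancy may be asked about more than once.

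Part of this stands. A reader might infer that the survey is the only point at which a pregnancy could come to light. The documents do not support that, since any of the later contacts might reveal one. They do support the narrower statement that none of those contacts is given that purpose, and that none could reveal a pregnancy the woman does not know about. The exclusion and the requests likewise cover intention and recognised pregnancy, not an unrecognised one.

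A reader might also infer that a late period gives no warning at all. That goes too far. Two of three diagnostic features suffice, so some women qualify with regular cycles, and short cycles also meet the menstrual feature.

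A reader might take the 16% to 66% for all 39 women over 4 weeks as the risk of exposing a pregnancy to the device. It is not. Only 13 women receive the device, that range uses the longest gap, and it treats every conception as unrecognised.

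Finally, the primary endpoints are feasibility, acceptability, credibility and safety measures, and recruitment, retention and adherence are to be reported descriptively. The validity argument therefore reaches secondary outcomes only.

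**Conclusion.** The point holds in this form: non-pregnancy is an entry criterion with a stated safety reason behind it, and the procedures as written include no objective or repeated verification of it before allocation. This follows from the text and depends on no assumed rate.

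The size does depend on assumptions. With a monthly conception probability of 0.5% to 3%, the chance of at least one conception between survey and allocation among the 13 device-arm women is about 3% to 17% for a 2-week gap and 6% to 31% for a 4-week gap. Recognition before Visit 1 would lower these figures. The upper end is generous because women planning pregnancy are excluded and non-hormonal contraception is not barred. Pregnancies already unrecognised at the survey would raise them.

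The case for change is mainly safety. The protocol does not contradict itself here; the criterion is simply not secured by the procedure meant to apply it.

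**What to change.** Reconcile sections 4.1.1, 5.3, 10.3 and Appendix 1 so that the existing criterion is verified before allocation:

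- Add a pregnancy assay to the Week -1 pathology request in Appendix 1, on blood that is already drawn.
- State in sections 5.3 and 5.5.1 that its result is seen together with the glucose tolerance result before the envelope is opened.
- State in section 7.1.1 and Appendix 1 that pregnancy status is asked again at Visit 1.

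The cost is one extra assay on about 40 samples and a few lines of text, with no extra visit or needle. The assay can miss a very recent conception; the repeat question narrows that gap but does not close it. The change does not address conceptions during the 12-week intervention, for which the protocol would still rely on its existing section 10.3 wording.
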